### Timeline patients’ assessment

The RGS@home RCT is a longitudinal study that recruits and assesses stroke patients at different time points after stroke (Fig. 3). All patients are evaluated on primary and secondary outcome measurements by trained clinicians (different from those that performed the baseline assessment) at the respective hospital.

**Fig. 3 Fig3:**
[figure not shown]
Clinical trial timeline. Participants are recruited as inpatients shortly after a stroke or as outpatients after hospital discharge. After a pre-selection, participants receive baseline evaluations and are randomly assigned to the intervention group or control group. The inpatients start using the RGS desktop setup during their stay at the hospital, while the outpatients use RGS directly in their homes. All participants in the intervention group are provided with a wearable device (RGSwear) for continuous monitoring. The control group receives rehabilitation as usual according to the standard care of the countries included in the study. According to the outcome measures assessments, all participants are evaluated again at 3, 6, and 12 months after baseline evaluation (see Tables 2 and 3)

### Study procedure: baseline measures and follow-up assessments

The participants’ characteristics are collected at baseline and include demographic data (age, gender, height, weight, address of rehabilitation center), social situation (marital status, social support at home, occupation status, educational level), and data related to their clinical history (date of stroke, lesion location, paretic side, dominant side). Tables 2 and 3 show the clinical scale used at baseline and at a follow-up to assess motor function, disability, activities of daily living, quality of life, and other measurements, covering the five domains of interest (see outcome measures).

We also collect data from the RGS setup, including the type of protocols selected, the time spent using the protocols, the kinematics obtained with the motion capture imagers, and the users’ performance. The data from the RGSwear wearable is also collected.

### Outcome measures

Outcome measures are collected at four time points during the study (see Fig. 3) and include measurements to assess disability and impairment as well as quality of life (see Table 2). Additional variables are collected via the eCRF (but not included in the trial registry) and include readmission, cost of treatment, quality of life, and acceptance (see Table 3).

#### Primary outcome measures

One main outcome measure is calculated as a compound score summarizing the main outcome of each of the 5 domains: (1) disability and impairment (Barthel Index for independence in activities of daily living), (2) readmission (number of patients who return to the hospital (inpatient) after being discharged to at-home status), (3) cost of treatment (total cost of the therapy), (4) quality of life (the Stroke Specific Quality of Life Scale), and (5) acceptability (amount of use at home).

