	Number and reason of dropouts				x		x
	Acceptability and usability Questionnaire for patients and physicians.				x	x	x
Quality of life	Stroke Specific Quality of Life scale (SSSQOL)				x		x
	Number of falls				x	x	x
	Short-Form-36 (SF-36)				x	x	x

^a^Included in the eCRF but not in the trial registry

**Table 3 Tab3:** Additional variables collected via eCRF

Assessment		3 months	6 months	12 months
Readmission	Number of outpatients that return to the hospital after discharge	x	x	x
	Reason for readmission	x	x	x
	Days of hospitalization due to readmission	x	x	x
	Costs of readmission	x	x	x
	Presence of CVA risk markers such as waist to hip ratio, smoking cessation, blood pressure, hypertension, and blood markers	x	x	x
Cost of treatment	Total cost of therapy	x		x
	Hours of therapy	x		x
	Total cost of traveling from home to hospital	x		x
	Hours of traveling from home to hospital	x		x
	Number of days of inpatient hospitalization	x		x
Quality of life	Return to work	x	x	x
	Number of formal caregiver hours per week	x	x	x
Acceptability	Number of hours of system use at home	x		x
	Number of hours technical/visits to patients’ home	x	x	x
	Number of equipment replacements	x		x
	Incidents related to use	x		x

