#### Secondary outcome measures

The secondary outcome of this study is the impact of stroke diagnosis on ADL involving the use of the upper limb. We use the Fugl-Meyer Assessment for Upper Limb (UE-FM), Barthel Index, and the Stroke Impact Scale to quantify these variables.

For the interaction with the RGS system, we measure the daily use, derived estimates of joint synergies, range of motion, reaching speed, precision, etc. (see [17] for details on the analyzed parameters). For the RGSwear, we analyze the daily use based on step count and accelerometer data.

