### Intervention and control groups

As explained in the “Allocation and blinding” section, patients are allocated in a randomized fashion either to the intervention group (RGS treatment plus rehabilitation as usual) or to the control group (standard care) (see Fig. 3 and Tables 2 and 3).

The *intervention group* follows a rehabilitation program for motor training using the RGS system at the clinic and home in addition to standard care. The training consists of various RGS-based exercises involving reaching, grasping, and placing virtual objects in a virtual environment. The training period and the number of training sessions are variable. They are set by the treating clinicians based on the patients’ needs and on dosage guidelines agreed by the three clinical partners in the trial (see the “Treatment dosage” section). Patients recruited at the subacute phase (inpatients) will receive the rehabilitation treatment via RGS at the hospital, from recruitment until discharge. In addition, the patients in the intervention group are prescribed occupational or physical therapy following the local clinical practice of the rehabilitation unit from admission to discharge. Patients recruited after discharge (outpatients) will train with RGS at their homes daily for 3 months, including weekends. All the patients in the intervention group (inpatient and outpatient) receive the RGSwear at recruitment for up to 1 year post-recruitment.

The *control group* receives standard care provided to patients after clinical discharge, which varies according to the patients’ condition and the different standards of care practiced in each EU country [18]. Also, at discharge, patients are provided advice for continuing voluntary rehabilitation in their homes. Given the huge regional variability, a detailed description of standard care is not reported in this study. In the footnote, we have provided the links to the National Health guidelines for Spain^1^, France^2^, and Sweden^3^.

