## Statistical method

We will perform mainly between-subject analysis by comparing the mean outcomes of the experimental group with the mean outcomes of the control group. To analyze the clinical outcomes related to disability and impairment, we will calculate the normalized improvement, which shows improvement or decline in proportion to the maximum score possible in the respective scale, therefore avoiding ceiling effects. Depending on whether the data is following a normal distribution, we will use parametric or non-parametric statistics. In the case of non-normal data, medians will be reported. We will perform an intention-to-treat analysis. The last observation carried forward analysis will be performed alongside a complete-case analysis to account for missing data.

To address the *primary outcome on disability and impairment*, a between-subject analysis will be used to compare the change in disability (Barthel Index (BI)) between the experimental and control groups at baselines 3, 6, and 12 months.

For the *secondary outcomes* on usability and impairment and other planned comparisons, we will perform the following analysis (for abbreviations, see Table 2):

Changes in independence (CAHAI), participation (SIS), depression (HDRS) fatigue (FSS), pain (VAS), spasticity (mAS), and impairment (BI and FM-UE) are analyzed from baseline to months 3 and 12.

We will also look at the change in grip force and correlate it with FM-UE, CAHAI, and BI from baseline to 3 months and 12 months. The outcomes of this measure are important to evaluate the clinical effectiveness of the RGS intervention to reduce disability and impairment. To measure quality of life, we compare the group changes in the quality of life (SSQOL) and well-being (SF-36) from baseline to 3 months and 12 months. We will also compare well-being (SF-36) at 6 months.

For the additional variables shown in Table 3, we will proceed as follows:

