*Readmission*: We compare between the groups the number of outpatients that return to the hospital after discharge to at-home status, including readmission due to complications unrelated to stroke, from baseline to 3, 6, and 12 months. We also compare the days of hospitalization and their associated costs. Here, we will take into account the presence of CVA risk markers as covarying variables. The readmission outcome is used to evaluate the effectiveness of the RGS intervention in reducing, or at least not increasing, a hospital’s readmission after discharge compared to standard care.

*Cost of treatment*: We compare the total cost of rehabilitation therapy/hour provided at the hospital or in the community and transportation costs/hour between the hospital and home at 3 months and after 12 months. We also compare days/hours of hospitalization and whether additional therapy, not replacing the RGS-based training (e.g., magnetotherapy, electrotherapy, thermotherapy), was provided. These outcomes allow us to evaluate the RGS’s effectiveness to reduce the cost of treatment.

*Quality of life*: We will compare between the groups the number of falls reported at 3 months and 12 months. In addition, we will compare how many patients were able to return to work and how many hours professional care was provided at 3 and 12 months. These outcomes facilitate the evaluation of the impact of the RGS ecosystem on quality of life and evaluate any risks arising from using the RGS system at home.

*Acceptance*: We will assess the RGS@home use (hours) after 3 months, 6 months, and 12 months. In both groups, we will keep track of the dropouts of the study. Specifically, in the intervention group, we will analyze the use of RGS at the hospital and home and the use of RGSwear. Concerning RGS@home, we will analyze the support needed (hours and visits to the patient’s home, replacement of materials, instructions, troubleshooting, etc.) and any incidents reported by the users. Also, we will analyze the patient’s evaluation of the System Usability Scale. The outcomes of this domain are important to evaluate the acceptance of the RGS ecosystem within the experimental group and the feasibility of the system for future use.

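### The stated primary outcome, a five-domain compound that includes home use of RGS, is not comparable between arms and does not match the analysis described, which compares Barthel change at three times

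*Protocol article*

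**What the plan says.** Primary outcome measures: "One main outcome measure is calculated as a compound score summarizing the main outcome of each of the 5 domains". The domains are disability (Barthel Index), readmission, therapy cost, stroke-specific quality of life, and "acceptability (amount of use at home"). Table 3 records the last as "Number of hours of system use at home", at 3 and 12 months.

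Intervention and control groups: the arms are "RGS treatment plus rehabilitation as usual) or to the control group (standard care"). Controls are not given the system.

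Statistical method: for the outcome labelled primary on disability and impairment, the plan is to "compare the change in disability (Barthel Index (BI)) between the experimental and control groups at baselines 3, 6, and 12 months". The paragraphs that follow take the secondary scales, readmission, cost, quality of life and acceptance one by one. The stated purpose of the acceptance domain is to "evaluate the acceptance of the RGS ecosystem within the experimental group". No step combines the domains.

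Secondary outcome measures: "We use the Fugl-Meyer Assessment for Upper Limb (UE-FM), Barthel Index, and the Stroke Impact Scale to quantify these variables". The Statistical method section also lists Barthel among the secondary analyses at months 3 and 12.

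**The concern.** The trial aims to show that RGS plus standard care is superior to standard care alone, so its main outcome must be measurable in the same way in both arms. Hours on a system that only one arm receives cannot be. Either a control has no score, or the control scores zero by design and the arms are pushed apart whatever happens to function, quality of life, readmission or cost.

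The analysis text does not settle the matter, because it never mentions the compound and gives the primary label to one of its components at three times. A reader of the final report could not tell which result was meant to carry the superiority claim. The risk is practical. The Data monitoring section lets the sponsor extract data four times a year for preliminary analyses, and the Discussion already reports that intervention patients use the system more than prescribed.

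**Working it through.** **1. Size and split.** Allocation and blinding gives 3 hospitals × (20 + 10) = 90, that is 60:30, which reproduces the stated total. (The abstract describes recruitment differently; that is a separate matter.) The sample size rests on feasibility. No significance level, power, effect or SD is given, so two-sided 5% is assumed below.

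**2. The texts side by side.**
- Outcome section: one compound that includes home use.
- Arms section: RGS in one arm only.
- Acceptance paragraph: assessed within the experimental group. By the article's own account this domain is not a between-arm outcome.
- Statistical method: no analysis of the compound; Barthel labelled primary for its domain, and also secondary.

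No choice of weights resolves this except a weight of zero on home use, which removes the component.

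**3. How far home use alone would separate the arms (illustration).** Assume an equal-weight mean of five z-scores, controls' use = 0, and no arm difference on the other four components. Scale use so that the RGS arm has mean 1 and SD equal to its coefficient of variation (CV). Let ρ be the correlation among the other four components.

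- Overall variance of use: (2/3)·CV² + (2/3)(1/3)
- Standardized arm difference in use: Δ = 1/√(that variance)
- Arm difference in the compound, in SDs: d = Δ/√(5 + 12ρ)

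| CV | ρ | Variance of use | Δ | d | Simulated share significant for RGS |
|---|---|---|---|---|---|
| 0.3 | 0 | 0.060 + 0.222 = 0.282 | 1.88 | 0.84 | 99% |
| 0.5 | 0.3 | 0.167 + 0.222 = 0.389 | 1.60 | 0.55 | 72% |
| 1.0 | 0.5 | 0.667 + 0.222 = 0.889 | 1.06 | 0.32 | 30% |

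In hours, the lower recommended time gives 24 min × 90 days = 36 h. With independent components and 15% readmission (assumed), the share is 97% for 40 h (SD 15), 91% for 36 h (SD 20) and 74% for 20 h (SD 20). With component correlation 0.5 these three settings give 43% to 73%. With independent components and therapy cost 0.5 SD worse under RGS, they give 80%, 61% and 33%.

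The 30% to 99% range does not combine high correlation with a cost penalty. Doing so in the last row of the table gives d ≈ (1.06 − 0.50)/√11 = 0.17. The standard error is √(1/60 + 1/30) = 0.224, so d/SE = 0.76 and P(Z > 1.96 − 0.76) ≈ 12%. Even that exceeds the 2.5% expected in favour of RGS under no effect.

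**4. Barthel at three times.** Suppose each time were tested at 5% and any one counted as success. Independent tests would give 1 − 0.95³ = 14.3%. At between-time correlations of 0.5, 0.7 and 0.9, simulation gives 12.5%, 10.9% and 8.3%. The article does not state this rule.

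**5. What one named test offers.** At 60:30 and 80% power, the detectable difference is (1.960 + 0.842) × √(1/30 + 1/60) = 2.802 × 0.2236 = 0.63 SD. With the 5% split equally over three times, it is about 0.72 SD.

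**The case against.** The label in the Statistical method section reads naturally as the first of the five domains, and the section then covers every domain in turn. On that reading Barthel has not replaced the compound; only the combining step is absent. This is fair, but it leaves the one declared main outcome without an analysis. It can also be said that weights, primary time point and multiplicity rules are commonly left to a full protocol or analysis plan. That stands, and their absence is not part of the point. The point rests on a component that controls cannot have and on two sections that disagree.

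Several stronger readings are tempting but not supported:
- A reader might infer that the trial has no valid primary comparison at all. A randomized comparison of Barthel change at any one named time would be valid.
- A reader might infer that a significant compound would show only that patients given RGS used it. The other four domains also contribute, and added therapy could move cost in either direction. The score would be uninterpretable, not purely a measure of use.
- Readmission is worded as a number of patients, but yes/no per patient is the obvious reading.
- Cost, stroke-specific quality of life and home use have no 6-month entry in the tables, but nothing says that the compound is calculated at 6 months.
- An inflated error rate for Barthel follows only if any of three tests counts as success, which is not stated.

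**Conclusion.** The point holds in this form: the stated primary contains a component that is zero or undefined for all controls, and the analysis section describes something else. This is wrong as written, not detail left out. The direction of the distortion follows from the design and needs no simulation. Its size does depend on assumptions. The 30% to 99% range rests on equal-weight z-scores, use scored 0 in controls, 60:30, two-sided 5%, equal results on the other domains, CV of use 0.3 to 1.0 and correlation 0 to 0.5. A cost penalty under RGS lowers the shares and, combined with high correlation, takes them below that range. The family-wise error of about 8% to 12.5% (correlation 0.9 to 0.5) is conditional on an unstated any-of-three rule. Because the trial is meant to support a superiority claim, this must be settled before the arms are compared further.

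**What to change.** Reconcile Primary outcome measures, Secondary outcome measures and Statistical method before any further by-arm outcome analysis, and disclose any by-arm analyses already made from the quarterly extractions.

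- Remove home use from the between-arm primary and describe it in the RGS arm only.
- Name one primary, measured the same way in both arms, at one time point. Barthel change from baseline to 3 months, the end of the intervention, is reasonable. A later time is also defensible given the stated aim of counteracting deterioration.
- Place the other Barthel times in a stated order as secondaries, and delete the duplicate Barthel listing.
- Report the remaining domains separately.
- If a compound is kept, limit it to patient-level components measured in both arms (for example Barthel and stroke-specific quality of life), and state how it is analysed.

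No new data are needed for the Barthel option: Table 2 schedules Barthel at baseline and at every follow-up. The cost is a protocol amendment and giving up the five-domain global claim.

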**Fig. 2 Fig2:**
[figure not shown]
The RGS platform and its use during the patient’s journey to recovery. The RGS grants a continuum of care and rehabilitation, monitoring, and analytics that supports clinicians in their decision-making (Medical Information Management System (MIMS)) and stroke patients (inpatients and outpatients) and with a “soft-landing” from the hospital to home

RGS@home is a multicentric study, and the trial is conducted in three different hospitals across Europe, namely, Spain, Sweden, and France. Thus, this study will also provide insights into whether the proposed system can be used independently of country-specific practice, standards of stroke care, and reimbursement systems. We hypothesize that the RGS setup combined with conventional therapy will be a more effective rehabilitation program than conventional therapy alone. More specifically, we expect the combined approach to show high adherence to treatment and higher effects on function and well-being, while costs will be reduced. A specific effect we seek to reveal is the positive feedback between rehabilitation, ADLs, and recovery, which we see as a process that can overcome deterioration which can be achieved with e-health solutions. We hypothesize that spontaneous use of the paretic limb, as measured with the RGSwear wearable, is predictive of recovery.

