## Method

### Study design

The RGS@home study is a randomized controlled trial (RCT) with stroke patients recruited from three hospitals in Spain, Sweden, and France. This RCT compares the impact of the intervention with the RGS platform plus standard care versus standard care alone. The standard care was provided to the patient as recommended in each hospital, on primary and secondary outcomes (see the “Outcome measures” section).

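### The pooled cost comparison across three countries has no stated hospital term, so between-hospital cost levels add noise and a chance hospital imbalance can show up as a cost difference

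*Protocol article*

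**What the plan says.** The section on primary outcome measures states: "One main outcome measure is calculated as a compound score summarizing the main outcome of each of the 5 domains". Its third domain is "3) cost of treatment (total cost of the therapy". Table 3 lists "Total cost of therapy" among the eCRF variables at 3 and 12 months, and hours of therapy as a separate item.

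The statistical method section says the analysis will mainly be between subjects, "comparing the mean outcomes of the experimental group with the mean outcomes of the control group". For cost it adds: "We compare the total cost of rehabilitation therapy/hour provided at the hospital or in the community and transportation costs/hour between the hospital and home". Neither statement mentions hospital or country.

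The trial has "stroke patients recruited from three hospitals in Spain, Sweden, and France". The study rationale expects to learn whether the system can be used "independently of country-specific practice, standards of stroke care, and reimbursement systems", which takes for granted that these differ. The section on intervention and control groups says standard care "varies according to the patients’ condition and the different standards of care practiced in each EU country".

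The allocation section plans 30 patients per hospital, 20 intervention and 10 control. It lists three minimisation conditions: time since stroke, age and severity. Hospital is not one of them.

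**The concern.** A patient's therapy cost is roughly hours used multiplied by a local price. Where price levels or usual amounts of therapy differ between hospitals, the hospital explains part of the spread in cost. A comparison of two overall means leaves that part in the error term. In a trial of 90 patients sized by feasibility, this can hide a real saving.

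The second issue is balance. The 20:10 split per hospital is a plan, and the listed minimisation conditions do not enforce it. If a dear hospital ends with more than its share of intervention patients, the intervention arm looks more expensive even when both arms use the same hours. The reverse imbalance looks like a saving. Either result would enter a domain of the primary outcome.

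**Working it through.** **The plan's own figures.** 3 × (20 + 10) = 90 and 60:30 = 2:1, as stated. The article gives no cost, price or cost SD, so everything below rests on assumed price ratios and an hours distribution that is the same in every hospital. The calculation is for total cost as hours × price.

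**1. Noise, with and without a hospital term.** Relative to the squared mean, the variance of pooled cost is (1 + CV_hours²)(1 + CV_price²) − 1. At one common price it is CV_hours². With stratification by hospital, still at local prices, it is CV_hours²(1 + CV_price²), a ratio of 1 + CV_price² to the common-price variance.

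- Prices 30/45/75 (1 : 1.5 : 2.5): mean 50, variance 350, CV_price² = 350/2500 = 0.14.
  - CV_hours 0.4: (1.16 × 1.14 − 1)/0.16 = 2.02, standard error up 42%.
  - CV_hours 0.8: (1.64 × 1.14 − 1)/0.64 = 1.36, standard error up 17%.
  - Stratified: 1.14, standard error up 7%.
- Prices 40/50/60 (1 : 1.25 : 1.5): CV_price² = 66.7/2500 = 0.027. Ratio 1.19 to 1.07 without a hospital term, 1.03 with one.

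**2. The same in terms of power.** Assume mean 100 hours, SD 40, a saving of 20 hours and two-sided 5%. Prices are scaled to mean 1. Power = Φ(20/SE − 1.96), with SE = SD × √(1/60 + 1/30).

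| Prices | SD, no hospital term | Power | SD, stratified | Power |
|---|---|---|---|---|
| 1 : 1 : 1 | 40.0 | 61% | 40.0 | 61% |
| 1 : 1.25 : 1.5 | 43.7 | 53% | 40.5 | 60% |
| 1 : 1.5 : 2 | 49.6 | 44% | 41.5 | 58% |
| 1 : 2 : 3 | 59.4 | 32% | 43.2 | 54% |

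The unstratified SD is √[(1 + CV_price²) × 40² + 100² × CV_price²]; the stratified SD is 40 × √(1 + CV_price²). Nearly all the loss comes from the missing hospital term rather than from local pricing.

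**3. Imbalance at equal hours.** Suppose the dear hospital ends at 22:8 and the others at 19:11.

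- Prices 30/45/75: (19×30 + 19×45 + 22×75)/60 = 51.25 against (11×30 + 11×45 + 8×75)/30 = 47.5, which is +7.9%.
- Prices 40/60/80: 61 against 58, which is +5.2%.
- With 20:10 everywhere the gap is exactly 0.

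If hospital is left wholly to chance (60 of 90 drawn at random), a hospital's intervention count has SD √(30 × 2/3 × 1/3 × 60/89) = 2.1. The SD of the price-only gap is then CV_price × √(1/60 + 1/30) × √(90/89): 6.1% of mean cost at 1 : 1.5 : 2 and 9.2% at 1 : 2 : 3. In simulation, 95% of such gaps lay within 11.7% and 17.5% respectively.

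**4. Type I error of the unadjusted test (simulation, 4,000 runs).** With 20:10 achieved it is 2.2% (1 : 1.5 : 2) and 0.9% (1 : 2 : 3), which is conservative. With hospital left to chance it is about 5%.

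**5. What a hospital term does not remove.** Let the arm difference in hours be +10, +10 and −15, the last in the dearest hospital. The mean is +1.7 hours. Weighted by price it is −1.1 (1 : 1.5 : 2) or −2.5 (1 : 2 : 3), so cost falls while hours rise. Only a comparison of hours alongside cost shows this.

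**The case against.** A reader might infer that the plan biases the cost comparison or manufactures a saving. The documents do not support that. The planned 20:10 in each hospital cancels price differences between arms, and without it the unadjusted test still holds its 5% level. The 22:8 split is an illustration. What remains is added noise, and a gap that chance can produce in one trial.

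A reader might also infer that costs will be entered at unadjusted local prices. The article does not say so. The source of unit prices, currency and price year commonly belong to a full protocol or economic plan, and their absence from an article is no finding. A hospital term may likewise stand in a document not shown. The point rests on what is stated: a comparison of means over three countries, and minimisation conditions that leave hospital out.

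Nor do the documents require a common price list. The hypothesis is that costs fall, and cost at actual local prices is a legitimate answer to that; common pricing answers a different question. Pricing readmission days into this domain would also count readmission twice, since it is a domain of its own.

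Finally, the scaling and weighting of cost within the compound score are not given, so the variance ratios apply to mean cost and cannot be carried over to the score. That objection stands.

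**Conclusion.** The point holds as a matter of precision and chance imbalance. The stated cost comparison ignores a factor that the article itself gives reason to think matters. At assumed price ratios from 1 : 1.25 : 1.5 to 1 : 2 : 3, power for a 20% saving falls from about 61% to between 53% and 32%; a hospital term restores it to between 60% and 54%, and also removes the price-only gap. If prices are nearly equal across the hospitals, the loss is small. These figures assume equal hours across hospitals; differing standard care would add between-hospital spread that the same term removes.

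One wording issue bears on this. The primary outcome section names total cost, whereas the statistical section can be read as cost per hour. Under that reading the measure is close to a local price, so the figures above would not describe it and the hospital would matter even more. The two passages should be reconciled.

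**What to change.** - Compare therapy cost between arms stratified by, or adjusted for, hospital.
- Do the same when forming the cost domain of the primary score, for example by standardising cost within hospital on both arms together.
- Compare hours of therapy, already in Table 3, alongside cost as the price-free measure of resource use.
- State whether the cost measure is total cost or cost per hour.
- Optionally, add a valuation at common unit prices as a sensitivity analysis, limited to therapy so that readmission is not counted twice.

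The cost is a few lines of analysis text and two degrees of freedom for three hospitals; no new data are needed. Standardising within hospital expresses the effect in hospital-specific SD units, so cost in money should still be reported. Only the optional analysis needs a price table. Table 3 has a single item for therapy hours, with no split by setting or type, so that valuation would be coarse.
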